##### Fixed-angle plate and screws vs standard-of-care (parallel cannulated screws)

No formal inference statistical analysis will be conducted on the data from the pilot arm of the study. The proportional primary event rate, mean estimates and variability of the secondary measures in the two groups will be described. Additionally an estimate of the size of the treatment effect due to the fixed-angle plate will be made to inform further study designs.

#### Subgroup analyses

Planned subgroup analyses will be undertaken only for fracture displacement (displaced vs undisplaced), dementia and appropriate age groups.

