## Methods

### Trial Design

#### Design summary

This trial will be a three arm single centre, standard-of-care controlled, double blinded, pragmatic, randomised clinical trial.

The study will include a standard two-way comparison between PRP and standard-of-care fixation versus standard-of-care fixation alone. This comparison will be the only hypothesis-testing analysis. In addition there will be a subsidiary pilot arm testing fixed-angle screw and plate fixation. This comparison will be a hypothesis-generating analysis only.

The trial is expected to last a total of two years. It is expected that participant recruitment will take one year and final follow-up will be at one year.

The trial was given ethical approval by the Coventry Research Ethics Committee on 6 May 2009.

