#### Power and sample size

The minimum clinically important treatment effect of PRP was agreed in discussion with several expert orthopaedic trauma surgeons. Although the figures varied by surgeon, all agreed that an absolute reduction of 15% in fixation failure would be clinically important. The overall rate of fixation failure of all intracapsular fractures of the femur is reported to be 20-35% [10]. Table 1 shows the total sample size with two-sided significance set at 0.05 for various scenarios of minimum clinically relevant difference. Sample sizes were determined using the PS power and sample size software [11].

**Table 1 T1:** Sample sizes calculated for various scenarios

Rate of failure in control group (%)	Rate of failure in the intervention group (%)					
	
	10		15		25	
	
	80% power	90% power	80% power	90% power	80% power	90% power
25	100	133				

30	62	82	121	161		

35	43	57	73	97	329	440

The mortality of patients with intracapsular fractures of the proximal femur is approximately 20% during the first year and this needs to be taken into account in the sample calculation. A recruitment target of 200 participants provides a good margin for unanticipated recruitment problems and loss to follow-up.

In the absence of an agreed method to determine the sample size for a pilot study a group of expert orthopaedic surgeons were consulted. All agreed that a sample of 25 participants in the fixed-angle screw and plate group would be sufficient to provide adequate pilot data.

From a recent audit carried out in our department we know that approximately 450 fractures of the proximal femur are treated operatively per year at University Hospital Coventry and Warwickshire. Approximately 250 of these patients would be eligible for inclusion into this trial. Therefore, even accounting for significant loss to follow-up, the trial sample can be recruited in one year.

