#### Treatment allocation

##### Sequence generation

The allocation sequence will be generated randomly. The randomisation will be weighted such that at the end of the trial there will be 25 participants in the fixed-angle screw and plate group and 100 participants in each of the remaining groups. Randomisation will be stratified by displacement of the fracture. Fractures will be defined as undisplaced (Garden grade I or II) or displaced (Garden grade III or IV); Garden's classification of intracapsular fractures is well recognised and universal and it has been validated to distinguish between grades I and II compared with III and IV [12,13]. The surgery will be performed by any of the 16 Consultant Surgeons, two Associate Specialists and 14 Trainees at the University Hospital Coventry and Warwickshire. The large number of surgeons and the wide skill mix should eliminate the 'surgeon effect' such that stratification by surgeon is not required.

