### Statistical analysis plan

#### Analysis of efficacy

##### PRP vs standard-of-care (parallel cannulated screws)

The primary outcome measure, the proportion of patients requiring re-operation for failure of fixation within one year of sustaining the fracture, will be analysed using a chi-squared test for differences between internal fixation alone (control) and internal fixation and PRP (PRP) on an intention-to-treat basis. Treatments will be considered to differ significantly if p-values are <0.05 (5% level). Similarly, chi-squared tests will be used to assess the significance of observed differences for the secondary proportional outcome measures. If the numbers in the contingency tables are small (cells with values below 10) then Fisher's exact test will be used in preference to the chi-squared test. In addition to the main analysis, that will report treatment group effects for the primary outcome measure, a subsidiary analysis will use a multiple linear regression model to investigate the relationship between each patient's EQ-5D Score at 12 months and the treatment arm, age, gender, dementia and fracture displacement for each patient. Estimates, and 95% confidence intervals, from the regression model, and unadjusted results from t-tests will be reported and inferences made on the significance of the treatment effect. All analyses will be based upon an intention-to-treat analysis so missing data due to protocol violations will not be relevant. The primary outcome measure in this study has been chosen in order to limit the possibility of losing data from failed participant follow-up. The primary measure can be sourced from the patient, relative, GP or national hp fracture database.

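### Age is to be split into subgroup bands that are left open; a treatment-by-age interaction with age kept continuous would serve better (low severity)

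*Protocol article*

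**What the plan says.** The Subgroup analyses section is one sentence: "Planned subgroup analyses will be undertaken only for fracture displacement (displaced vs undisplaced), dementia and appropriate age groups". Displacement has two levels, which the Sequence generation section defines by Garden grade. Age is to be grouped, but no boundary or number of groups appears anywhere in the article. No method is named for any subgroup analysis.

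Two other places bear on this. The Design summary says of PRP against standard fixation: "This comparison will be the only hypothesis-testing analysis". The efficacy section for that comparison lists age, dementia and displacement as covariates in a regression of the 12-month EQ-5D score, with no grouping of age mentioned. Individual ages will therefore be available to the analyst.

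**The concern.** The sentence presents a closed list, yet one of its three entries is not determined. *Appropriate* can be read after the data are in, and several sets of age bands could be defended at that point. Looking at several and keeping the most striking one is a multiple-testing problem that the reported p-value does not show.

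The second issue is separate and remains even if the bands are fixed in advance: cutting a continuous variable into groups throws away the ordering within each group.

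At stake is a claim that PRP helps only younger or only older patients. The Inclusion criteria section says the trial admits a broad population so that its conclusions apply widely, so a spurious age limit would work against that aim.

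**Working it through.** **Inputs from the protocol.** Group size: "100 participants in each of the remaining groups", so 200 in the PRP comparison. Two-sided 5% level: "Table 1 shows the total sample size with two-sided significance set at 0.05 for various scenarios of minimum clinically relevant difference". Event rate: "The overall rate of fixation failure of all intracapsular fractures of the femur is reported to be 20-35" per cent. First-year mortality is about 20%, so a sensitivity case uses 200 × (1 − 0.20) = 160.

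**The plan's own figures.** The protocol gives no error rate or power for subgroups; Table 1 is its only sample-size calculation. With n = [1.96√(2p̄(1−p̄)) + z√(p₁(1−p₁)+p₂(1−p₂))]² / (p₁−p₂)², for 25% against 10%:

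- 80% power: (1.96 × 0.5374 + 0.8416 × 0.5268)² / 0.0225 = 99.5, so 100.
- 90% power: (1.96 × 0.5374 + 1.2816 × 0.5268)² / 0.0225 = 132.8, so 133.

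All twelve entries reproduce, but as numbers per group, although the text calls them totals. That is a separate labelling matter. Here it only confirms the test settings.

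**Step 1: false positives if the cut is chosen from the data.** Simulation with no treatment effect and no interaction: 20,000 trials per setting, 200 or 160 participants, 1:1 allocation, event rate 20%, 27.5% or 35%. At each cut the interaction statistic is |log OR₁ − log OR₂| / √(v₁ + v₂), where v is the sum of 1/(cell + 0.5). The largest value over the candidate cuts is compared with 1.96. The number of candidate cuts is an assumption.

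| Age cuts considered | False-positive rate | Multiple of 5% |
|---|---|---|
| One, fixed at the median | 4.3-5.0% | 1 |
| 3 (quartiles) | 9.2-11.4% | about 2 |
| 5 | 12.2-15.8% | 2.4-3.2 |
| 9 (deciles) | 15.2-20.8% | 3.0-4.2 |
| 17 (10th to 90th centile, steps of 5) | 19.9-26.5% | 4.0-5.3 |

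The simulation standard error is at most √(0.265 × 0.735 / 20,000) = 0.3 percentage points. A check with 100 per arm and an assumed age distribution (mean 79, SD 10) gave 5.0% for a continuous-age interaction, 4.1% at one fixed cut and 14.6% for the best of five cuts.

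**Step 2: information lost by grouping.** If the treatment effect on the log-odds scale is linear in age, the efficiency of a grouped analysis is about the between-group share of the variance of age, Σ pₖmₖ², where mₖ is the standardised mean age in group k. The protocol gives no age distribution, so two shapes are used.

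- Median split, normal age: 2/π = 0.637, a loss of 36%.
- Median split, uniform age: (0.25 / 0.2887)² = 0.75, a loss of 25%.
- Tertiles, normal age: 0.793, a loss of 21%.
- 20/80 split, normal age: 0.490, a loss of 51%.

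**Step 3: what this means for power.** Under the assumed age distribution and a re-operation rate of 25-30%, simulated power for an interaction slope of 0.5 in log odds per 10 years was 27% with continuous age against 18-19% with a cut at 80. For a slope of 0.8 it was 57-58% against 38-41%.

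The gap agrees with step 2. A power of 27% corresponds to an expected z of 1.96 − 0.613 = 1.347. Multiplying by √0.637 = 0.798 gives 1.075, and Φ(1.075 − 1.96) = 19%. Starting from 57%: 2.136 × 0.798 = 1.705, and Φ(1.705 − 1.96) = 40%.

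The relation is symmetric. If the truth is a step exactly at the cut, the grouped analysis has the advantage: 27% against 19% for continuous age.

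**The case against.** The strongest reply is that this is one sentence in a condensed article. Age boundaries and the subgroup test are details that an article commonly leaves to the full protocol or analysis plan, neither of which is shown. That stands: undefined bands or an unnamed test would not, alone, be a finding. What remains is the choice the sentence does make, to group age, for which a better method exists using data already planned for collection.

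A reader might infer that the plan rejects an interaction test and will test PRP separately inside each subgroup, because "chi-squared tests will be used to assess the significance of observed differences". The documents do not support this. That sentence concerns the secondary proportional outcomes and says nothing about subgroups, and the same section also plans a regression containing all three subgroup factors. Separate tests in two fixed age groups would give a false positive in about 10% of trials (1 − 0.95² = 9.75%; simulated 9.5-10.5% with chi-squared tests), but the plan does not state that it will do this.

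The Design summary also limits the damage. Its direct contrast is with the pilot arm, but on its wording subgroup results are not confirmatory, and the list of subgroups is restricted to three factors. Finally, pre-specified bands with an interaction test are valid and hold the error rate near 5%. Preferring continuous age is then a matter of efficiency rather than validity.

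**Conclusion.** The point holds in a narrow form. The plan categorises age and leaves the bands open. If they were chosen after outcomes are seen, the false-positive rate for age would be roughly 10-25% instead of about 5%. No single multiple should be quoted, because it depends on how many cuts are assumed to be tried. With one cut fixed in advance there is no inflation. The 25-36% information loss rests on a near-linear age effect and an assumed shape for the age distribution.

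A reader might go further and conclude that a false age-specific claim is to be expected even if PRP does nothing. The figures do not bear that out: such a claim is a raised risk that stays well below one half. Nor do the documents say that the boundaries will follow the data. The primary comparison, sample size and trial conduct are unaffected. Low severity.

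**What to change.** In the Subgroup analyses section, replace the reference to age groups with a treatment-by-age interaction in a logistic model for the primary outcome, with age continuous. Report the interaction estimate with its 95% confidence interval and the fitted treatment effect at ages fixed in advance, labelled exploratory. Use the same interaction approach for displacement and for dementia, one factor at a time. If results by age band are also wanted for display, fix the boundaries before unblinding. If a fuller plan already does this, the article's sentence need only say so.

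The cost is a few lines of text and three model fits, with no new data. The small downside is that a linear age trend is assumed, so power is lower if the true effect is a step at a band boundary. An added quadratic term can check the linearity.

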#### Analysis of adverse events

The number and temporal pattern of adverse events will be investigated to assess if these differ between treatment groups.

### Trial organisation and oversight

#### Trial steering committee

A trial steering committee will be convened and independently chaired in accordance with the University of Warwick Clinical Trials Unit standard operating procedures. In addition to the independent chair, Mr [name], Mr [name], Dr [name] and Dr [name] will form the committee. All issues pertaining to the management of the trial will be co-ordinated by the trial steering committee. The schedule for meetings of the committee will be as follows:

Meeting 1: Trial commencement

Meeting 2: Interim meeting at 50% recruitment

Subsequent meetings: End of trial

#### Data monitoring committee

A data monitoring committee will be convened once the trial is 50% recruited. The committee will be chaired by Mr [name], University Hospital Coventry and Warwickshire NHS Trust.

#### Trial registration

The trial is registered with the Current Controlled Trials register ISRCTN49197425. The trial has been adopted by the National Institute for Health Research Clinical Research Network Portfolio NIHR CRN Study ID: 7762.

#### Project timetable and milestones

Trial recruitment commenced August 2009

All participants recruited August 2010

Trial completed August 2011

Trial reported December 2011

#### Unblinding

The blind will only be broken for clinical management purposes. In exceptional circumstances beyond this agreement will be sought from the Chief Investigator and statistician before the blind is broken.

#### Interim analysis

There will be no formal interim analysis conducted.

#### Indemnity/compensation/insurance

All issues of indemnity, compensation and insurance are detailed in the joint sponsorship agreement between the University of Warwick and University Hospital Coventry and Warwickshire NHS Trust.

#### Essential documents

All essential documentation will be stored as specified under the guidance from the clinical trials unit.

#### Monitoring and quality assurance policy

The Chief Investigator and data entry technician will conduct sampling of the database quarterly in order to identify any problems in trial procedures.

#### Dissemination and publication

The results of this trial will be disseminated to the trauma and orthopaedic surgery community via presentations at national and international meetings as well as publication in peer reviewed journals.

